#### Hypothesis

1a: A larger dose of pre-exposure, compared to a smaller dose, will increase engagement of the target mechanisms (expected relevance and attention). Hypothesis 2a: Compared to pre-exposure with only the target stimulus, compound pre-exposure will lead to stronger engagement of the target mechanisms of expected relevance and attention.

For Hypotheses 1a and 2a, changes expected in the candidate mediators should first be observed during the pre-exposure phase. To test these hypotheses during this phase, a two factor repeated measures MANOVA with one-between (pre-exposure group) and one-way within-subjects (trial) factor will be conducted separately for the variables expected relevance and attention. A significant group × trial interaction indicates that mean responses across trials is not the same for each group. If the interaction is present, follow-up analyses will focus on examining the plots of the mean change for each group and testing the degree to which the mean change from first to last trial differs between the groups. For the conditioning phase, a three-way repeated measures MANOVA will be conducted separately for each of the target mechanisms (expected relevance and attention). For these models, pre-exposure groups will serve as the between-subjects factor with stimulus and trial being the within-subject factors, and the analysis model will assess the main effects of each variable, as well as all-two-way and three-way interactions. Follow-up analyses depend on the nature of effects that are present (e.g., type of interactions or main effects). We expect that differences between pre-exposure groups will be greater—particularly at the early trials for stimulus CS^+^ _P_ —than for the other stimulus conditions. As such, follow-up analyses will focus on the degree to which means differ by pre-exposure group and stimulus type for each trial using a Bonferonni-adjusted alpha, as well as examining plots of the mean response by stimulus type and trial for each pre-exposure group.

#### Hypothesis 3

Higher pain sensitivity scores will be associated with increased engagement of the target mechanisms of expected relevance and attention.

To test the third hypothesis, individual differences in pain sensitivity will be included in the above analyses as a moderating variable. This will be done by testing interactions between pre-exposure and pain sensitivity.

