### Procedures

Participants will experience the virtual reality “game” seamlessly each visit however, the task has four discrete phases: pre-exposure, conditioning, and learning recall phases, all occurring in Visit 1, and a learning retention phase, which occurs in Visit 2. Next, we describe the four phases, explaining the trials in each phase.

Trials in the first phase, the *pre-exposure phase*, will begin with a minimum of six seconds in which the participant is free to navigate around the planet surface to collect fuel concealed in the landscape. Following the initial trial segment, the CS^+^ _P_ is automatically presented, accompanied by a fuel canister, at the first opportunity. The CS^+^ _P_ will be an alien stimulus that displays small vertical movements and associated individualized noises. The CS^+^ _P_ and the fuel canister will appear at a fixed distance from the participant and will be present for the remaining six seconds of the trial. Thus, each trial consists of a six second segment without the CS^+^ _P_, followed by a six second segment with the CS^+^ _P_. During pre-exposure, the CS^+^ _P_ is never accompanied by the UCS.

It is during the *pre-exposure phase* that the two between-subject independent variables are manipulated. First, the number of pre-exposure trials constitute the *pre-exposure dose* independent variable and will be either 12 trials (low dose) or 24 trials (high dose), based on random assignment. Second, for participants in the *single stimulus pre-exposure type condition*, the CS^+^ _P_ will always present in the environment without another alien stimulus. For participants in the *compound stimulus pre-exposure type condition*, a second novel alien stimulus will be immediately adjacent to the CS^+^ _P_ with the presentation period identical to that of the CS^+^ _P_ on the second half of the pre-exposure trials: the final 6 trials for those in the low dose condition, and the final 12 trials for those in the high dose condition.

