### Statistical analysis plan

SPSS software will be used to address Hypotheses 1a, 2a, and 3 described below. Mplus software will be used to address the remaining hypotheses. Note that throughout the analyses, an interaction between the two between-subjects factors is not of primary interest [25]. Rather, we anticipate that a particular combination of the groups, or the focal group, (i.e., high dose and compound condition) will have more favorable responses than each of the other groups. Consequently, we treat these between-subjects factors as one factor with four groups. Note that representing the four cells of the between-subjects factors in this way yields the same fit as a full between-subjects factorial model and readily enables us to assess the comparisons between the focal and other groups.

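### The pre-exposure group × trial MANOVA does not fit series of 12 and 24 trials: indexed by trial number it loses the low-dose groups or compares three groups treated alike, and it gates the useful follow-up

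*Protocol article*

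**What the plan says.** Under Procedures, the number of pre-exposure trials "will be either 12 trials (low dose) or 24 trials (high dose), based on random assignment". In the single-stimulus condition the pre-exposed alien "will always present in the environment without another alien stimulus". In the compound condition a second alien is added on "the final 6 trials for those in the low dose condition, and the final 12 trials for those in the high dose condition".

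Under Statistical analysis plan, dose and novelty are merged: "we treat these between-subjects factors as one factor with four groups". The expectation is that "the focal group, (i.e., high dose and compound condition) will have more favorable responses than each of the other groups". SPSS is named for Hypotheses 1a, 2a and 3.

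For the pre-exposure phase, the test of Hypotheses 1a and 2a is "a two factor repeated measures MANOVA with one-between (pre-exposure group) and one-way within-subjects (trial) factor will be conducted separately" for each mediator. It is read through the interaction: "A significant group × trial interaction indicates that mean responses across trials is not the same for each group". Only if that interaction is present do the follow-ups run, namely plots of mean change by group and "testing the degree to which the mean change from first to last trial differs between the groups". The article does not say which trials make up the trial factor, or which trial counts as last when series differ in length.

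**The concern.** A repeated measures MANOVA needs the same set of repeated measurements on every participant. Here the length of the series is itself one of the randomised factors. Trials 13-24 do not exist for the low-dose groups; they are not missing data that could be recovered or imputed.

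The article expects mediator changes to appear first in this phase, so this is the first look at the mechanism. If the omnibus test cannot register the dose or focal-group effect, a null result says little about the hypotheses, yet it closes the gate on the follow-up that could have addressed them. A positive result could be taken as support for the focal group when it came from another group. Hypothesis 3 is affected too, because pain sensitivity is to be added as a moderator to these same analyses.

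**Working it through.** **Inputs.** Trial counts and timing of the second alien: Procedures. Model, gate and follow-up: Statistical analysis plan, Hypotheses 1a and 2a. Total sample 180: Participants. The allocation ratio is not given; equal allocation, 180 / 4 = 45 per group, is assumed. The article does not give the inputs to its power analysis, so 180 is not reproduced here. The point does not depend on it.

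**Step 1: schedules** (S = pre-exposed alien alone, C = with the second alien).

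| Group | Trials 1-6 | Trials 7-12 | Trials 13-24 |
|---|---|---|---|
| Low dose, single | S | S | none |
| Low dose, compound | S | C | none |
| High dose, single | S | S | S |
| High dose, compound (focal) | S | S | C |

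**Step 2: trial factor with 24 levels.** Only the two high-dose groups have complete data. Participants retained: 2 × 45 = 90 of 180. Two of four groups remain and no dose comparison is possible.

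**Step 3: trial factor with the 12 shared levels.** All four groups enter. Trials on which treatment differs:

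- focal versus low-dose single: 0 of 12
- focal versus high-dose single: 0 of 12
- low-dose single versus high-dose single (dose, single stimulus): 0 of 12
- focal versus low-dose compound: 6 of 12 (trials 7-12)

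In the last comparison it is the low-dose group that has the second alien and the focal group that does not yet have it. Pooling over novelty does not help: a high-versus-low difference over trials 1-12 could arise only from the second alien in the low-dose compound group.

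**Step 4: simulation of step 3.** Assumptions: 45 per group; between-person and residual SD 0.7 each; the same decline over trials in every group; a shift of 0.3, 0.5 or 0.8 on trials with the second alien. Wilks' lambda was applied to the 11 successive differences over trials 1-12, with 2,000 runs. Share of runs rejecting at 5%:

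| Comparison (group × trial) | 0.3 | 0.5 | 0.8 |
|---|---|---|---|
| All four groups | 0.547 | 0.991 | 1.000 |
| Focal vs low single | 0.046 | 0.049 | 0.051 |
| Focal vs high single | 0.043 | 0.050 | 0.053 |
| Focal vs low compound | 0.543 | 0.985 | 1.000 |

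The simulation error on a true 5% rate is √(0.05 × 0.95 / 2000) ≈ 0.005, so both focal-versus-single rows agree with the false-positive rate at every effect size. The omnibus test rejects often, but only because of the low-dose compound group. The rejection rates depend on the assumed effects and SDs. The counts in step 3 do not.

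**Step 5: the follow-up.** If last means each group's own last trial (12 or 24), the change score exists in all four groups and covers the full manipulation. It is nevertheless reached only through the interaction in steps 2 and 3.

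**The case against.** The strongest reply is that the article never says the trial factor uses raw trial number. The series could be aligned by relative position: with 24 / 12 = 2, each low-dose trial would match a pair of high-dose trials, and the second alien would enter at position 7 of 12 in both compound groups. That layout is complete and computable. The article is also condensed, and a fuller plan may define the alignment. This stands in part. Re-indexing is not excluded, so a reader who infers that the four groups cannot be compared in this phase at all goes further than the text allows. But the article names a model with trial as the factor and states no re-indexing. As written, the model does not fit the design, which is more than an omitted detail.

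A reader might also infer that Hypotheses 1a and 2a are left without a sound test. They are not. The conditioning-phase MANOVA covers the same mediators with 12 trials per stimulus in every group, and nothing makes it depend on the pre-exposure result. Nor is misattribution of a positive result certain: the planned plots by group would probably show a pattern confined to the low-dose compound group.

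Finally, one might think a mixed model on all available trials cures the problem. It accepts unequal series, but it still has no low-dose data after trial 12, and at matched trial numbers the single-stimulus groups differ in nothing. By itself it gives no dose contrast.

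**Conclusion.** The point holds for the pre-exposure phase. With trial indexed by number, the planned MANOVA either discards both low-dose groups or tests an interaction in which three of the four groups, the focal group among them, have the same history by design. The informative follow-up is gated on that test and its last trial is undefined.

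The size is 2 of 4 groups lost under 24 levels (90 of 180 under assumed equal allocation), or 0 of 12 trials separating the focal group from either single-stimulus group under 12 levels. The second result assumes that groups are handled alike until their schedules diverge; the article describes no other difference. The damage is confined to this phase and to the moderator analysis built on it. The conditioning-phase test is unaffected.

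**What to change.** 1. Replace the gating omnibus test with a planned, ungated four-group comparison of each participant's change from the first to their own last pre-exposure trial (trial 12 or 24), with contrasts of the focal group against each other group.
2. Name the first presentation of the pre-exposed stimulus in conditioning as the equal-footing test of Hypotheses 1a and 2a. All four groups see it alone there. Define it by stimulus, because trial order in that phase is pseudo-random. This matters most for attention: at the last pre-exposure trial the compound groups view two aliens and the single-stimulus groups one, so a change in dwell time mixes learning with a different display. The mediation analysis already takes its mediator scores from the start of conditioning.
3. Keep any mixed model over all trials as a description of the trajectories, and state that trials 1-12 carry no dose information in the single-stimulus groups.
4. If alignment by blocks or relative position is what is intended, write it down before the pre-exposure data are analysed.

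The cost is minor rewording and one extra planned set of contrasts, in software already named. No new data are needed.

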## Methods

### Participants

This is a multisite study, with participants enrolled at universities in south Texas and northwest Ohio. For the United States, the region surrounding the Texas site has a larger than average Hispanic population [30], whereas the region surrounding the Ohio site has a substantial African American population [30]. The sites are therefore expected to provide opportunity to recruit Hispanic and African American participants– populations that are of greater risk for dental anxiety and poor oral health [10, 11].

Community volunteers between the age of 6 and 35 will be recruited using strategies such as a study Facebook page, ads posted in social media, newspapers, email announcements, and flyers at community sites. The sample size of 180 participants was determined by an a priori power analysis. Table 1 provides the inclusion/exclusion eligibility criteria for participation. The study will consist of two in-person visits, scheduled approximately 1 week apart, with participant remuneration of a $50 gift card per visit. The Institutional Review Board of the primary institution approved the research.

**Table 1 Tab1:** Inclusion and exclusion criteria

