The *conditioning phase* will consist of 36 trials (12 CS^+^ _P_ trials, 12 CS^+^ _NP_, and 12 CS^-^ trials) occurring in a pseudo-random order. The structure of the conditioning trials is the same as the pre-exposure trials, with the key exception that 75% of CS^+^ _P_ trials, and 75% of CS^+^ _NP_ co-occur with a dental startle UCS (see stimulus material section below). The dental startle UCS will be delivered through a fitted mouthpiece during the last 100ms of the trial with the alien and startle stimulus co-terminating. The dental startle stimulus will never be delivered on CS^-^ trials.

Immediately following the conditioning trials will be the fear *recall phase*, which is a series of 12 trials (4 CS^+^ _P_ trials, 4 CS^+^ _NP_, and 4 CS^-^ trials). The structure of the trials in this phase will be the same as in the prior two phases. During this phase, the dental startle UCS will not accompany any of the alien stimuli.

The trials in the fear *retention phase*, occurring at least 7 days later, are the same as those in the fear recall phase.

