### Study measures

#### Mediating variable measures

*Expected relevance* will be measured after the onset of the CS^+^ _P_, CS^+^ _NP_, or CS^-^ but prior to the onset of the UCS. To obtain ratings of the probability of a negative event occurring, participants will be presented the question “How likely is it something bad is about to happen?” and provide a response on a 10-point scale. The question will appear in front of participants in the virtual environment and ratings will be made using a hand controller.

*Attention* will be assessed with software in the Vive Pro headset that tracks eye movements to create a measure of dwell time.

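### The conditioning-phase repeated-measures MANOVA needs up to 36 complete values per participant, so unless gaps are filled beforehand even a small trial-level loss could remove a sizeable share of the sample

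*Protocol article*

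**What the plan says.** The Statistical analysis plan section fixes the software: "SPSS software will be used to address Hypotheses 1a, 2a, and 3 described below". It also merges the two randomised factors: "we treat these between-subjects factors as one factor with four groups".

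Under Hypotheses 1a and 2a, the conditioning-phase method is fixed as well: "a three-way repeated measures MANOVA will be conducted separately for each of the target mechanisms (expected relevance and attention". In that model "pre-exposure groups will serve as the between-subjects factor with stimulus and trial being the within-subject factors". The planned follow-up compares means by group and stimulus type at each trial. Hypothesis 3 adds pain sensitivity as a moderator to the same analyses.

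The Procedures section says the conditioning phase "will consist of 36 trials (12 CS^+^ _P_ trials, 12 CS^+^ _NP_, and 12 CS^-^ trials". Under Mediating variable measures, expected relevance is rated by hand controller after the stimulus appears and "prior to the onset of the UCS. To obtain ratings of the probability of a negative event occurring, participants will be presented the question". Attention is a dwell time from the headset's eye tracking. On size, the Participants section says: "The sample size of 180 participants was determined by an a priori power analysis".

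The article states no expected loss of trial values and no dropout rate. It mentions neither listwise deletion nor imputation.

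**The concern.** A repeated-measures MANOVA treats each participant as one row with one column per within-subject cell. A row with an empty cell cannot enter. That is a general property of the method and of the SPSS procedure, not something the article says. With 36 columns, the chance that a row is complete falls quickly as the loss rate per value rises.

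Some loss is plausible here. The rating is made inside a virtual-reality game by participants from age 6 upward, and eye tracking can fail on single trials. A participant with 35 usable values out of 36 would then contribute nothing.

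At stake is the precision of the tests for Hypotheses 1a, 2a and 3, and how well the analysed participants represent those randomised. The mediation models for Hypotheses 1b and 2b do not use the 36-cell layout. They are touched only indirectly: whether they are fitted separately by stimulus depends on the interactions found under 1a and 2a.

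**Working it through.** **Inputs from the Protocol article**
- N = 180 (Participants); 4 groups (Statistical analysis plan), so 180 / 4 = 45 per group if the groups are equal, which is an assumption.
- Cells per mediator: k = 3 stimuli × 12 trials = 36 (Procedures and Hypotheses 1a/2a), if every trial yields a value.

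**Inputs not in the article**
- The loss rate per value, p. The range 0.1% to 5% is shown.
- The degree of within-person clustering, as an intraclass correlation (ICC). The range 0.01 to 0.5 is shown.

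**The plan's own figure.** The 180 cannot be reproduced, because the article gives no alpha, power, effect size or dropout. It is taken as given.

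**Step 1: independent losses.** Share dropped = 1 − (1 − p)^k. For p = 1% and k = 36: 1 − 0.99^36 = 1 − 0.6964 = 0.3036. Complete cases: 180 × 0.6964 = 125.4, or 125.4 / 4 ≈ 31 per group.

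| Loss per value | Dropped, k = 36 | Complete of 180 | Dropped, k = 12 |
|---|---|---|---|
| 0.1% | 3.5% | 174 | 1.2% |
| 0.5% | 16.5% | 150 | 5.8% |
| 1% | 30.4% | 125 | 11.4% |
| 2% | 51.7% | 87 | 21.5% |
| 3% | 66.6% | 60 | 30.6% |
| 5% | 84.2% | 28 | 46.0% |

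The last column covers the case in which only 12 values per participant enter, since the article does not say outright that both mediators are obtained on every trial.

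**Step 2: losses clustered within persons.** Let each person's loss probability follow a beta distribution with mean 1%, with a = 0.01 × (1/ICC − 1) and b = 0.99 × (1/ICC − 1). Then P(complete) = B(a, b + 36) / B(a, b), where B is the beta function. For ICC = 0.10, a = 0.09 and b = 8.91.

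| ICC | Dropped, k = 36, p = 1% | Complete of 180 |
|---|---|---|
| 0.01 | 26.6% | 132 |
| 0.05 | 18.6% | 147 |
| 0.10 | 13.9% | 155 |
| 0.20 | 9.3% | 163 |
| 0.50 | 4.1% | 173 |

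**Step 3: what this means for power.** Take a two-group contrast with 80% power at 45 per group (two-sided 5%, normal approximation; all assumed for scale). The standardised difference is (1.960 + 0.842) × √(2/45) = 0.591.
- At 31.3 per group: 0.591 / √(2/31.3) − 1.960 ≈ 0.38, so power is about 65%.
- At 155 / 4 = 38.75 per group (ICC 0.10): 0.591 / √(2/38.75) − 1.960 ≈ 0.64, so power is about 74%.

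**Step 4: size of the alternative's covariance.** An unstructured matrix over 36 occasions has 36 × 37 / 2 = 666 parameters, so a mixed model needs a more parsimonious structure.

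**The case against.** The strongest reply is that the article names a model and does not say that incomplete participants are discarded. Imputation before the MANOVA is compatible with the text, and missing-data rules are commonly left to the full protocol or analysis plan. This stands: the absence of such a rule is not the point here, and the deletion has to be stated conditionally.

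A reader might infer that the plan will lose about 30% of its sample. The article does not support that. The figure needs a 1% loss rate, a value on all 36 trials and independence across trials, none of which is stated. Plausible causes such as age, distress or poor tracking act on the person, so losses would cluster and the share would fall below 30%.

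A reader might also infer that the randomised comparison is biased. Nothing in the article indicates that loss would differ between the four groups. Loss that is alike across groups and unrelated to the response costs precision and generalisability only. Nor can every awkward trial be counted as lost: looking away from the stimulus gives a low dwell time, which is a valid value, and the article does not say that a late rating is discarded.

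Finally, MANOVA leaves the within-person covariance unrestricted, which is a real merit. A mixed model gives that up in practice, and it does not cure loss that depends on the unobserved response.

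What remains is that the stated method is fragile by construction with this many cells, and that a less fragile one is available in the same software.

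**Conclusion.** The point holds in conditional form. Unless missing values are handled first, the conditioning-phase MANOVA for each mediator uses only participants complete on up to 36 cells. At an assumed 1% loss per value, up to about 30% of participants would be dropped if losses are independent, and about 4% to 27% if they cluster within persons over the ICCs tried. With 12 values and independent losses it would be about 11%. The arithmetic is firm; the loss rate, the number of values and the clustering are assumptions.

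The consequence is reduced precision and a less representative analysed sample for Hypotheses 1a, 2a and 3. Bias in the randomised contrasts would need loss that differs by group or depends on the response, which the article does not show. This is an inexpensive improvement worth making, not evidence that the analysis is invalid.

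**What to change.** Replace the conditioning-phase MANOVA with a linear mixed model for each mediator (SPSS MIXED, REML), containing the same group, stimulus and trial main effects and all their interactions. Fit it to all available trials from all randomised participants with data. Pre-specify a parsimonious within-person covariance structure and a simpler fallback in case of non-convergence. Take the planned group-by-stimulus contrasts at each trial from this model, and add the pain-sensitivity interactions to it for Hypothesis 3.

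The cost is a change of wording in the analysis plan; hypotheses, data collection and software stay the same. There are two downsides. The covariance structure must be chosen in advance, and a poor choice affects standard errors and tests. Validity also rests on values being missing at random, so the amount and pattern of trial loss should be reported by group.

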### Experimental design

The study will use a mixed design, with two within-subject independent variables and two between-subjects independent variables, and one measured continuous moderator variable. One within-subjects variable is stimulus type [stimulus type: pre-exposed to-be conditioned stimulus (CS^+^ _P_), non-pre-exposed to-be conditioned stimulus (CS^+^ _NP_), and an unpaired control stimulus (CS^−^)]. The second within-subjects variable is time [trial number]. One of the two-level between-subjects independent variables is pre-exposure dose [12 trials vs. 24 trials]. The second two-level between-subjects independent variable is pre-exposure novelty [single stimulus vs. compound stimuli]. Participants will be randomly assigned to one of the four between-subject conditions using the randomization feature in the software Research Electronic Data Capture (REDCap; 31, 32). Randomization will be done in session to obtain allocation concealment [33]. The continuous moderator variables are two individual-difference measures of pain sensitivity.

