### Stimulus material

#### Alien images

Novel alien stimuli were developed and pilot tested with children, adolescents, and adults to obtain stimuli that were perceived as relatively neutral, yet distinct. To reduce any potential influence of specific alien stimuli on study outcomes, three alien stimuli will be counterbalanced for the CS^+^ _P_, CS^+^ _NP_, and CS^-^. The compound alien stimulus will be held constant.

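### The conditioning-phase model leaves out the alien-to-role assignment, so any stable difference between aliens adds to the error of the group × stimulus test: a minor, cheaply recovered loss of power

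*Protocol article*

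**What the plan says.** Under Stimulus material (Alien images), the article explains why the aliens are rotated: "To reduce any potential influence of specific alien stimuli on study outcomes, three alien stimuli will be counterbalanced for the" three stimulus roles. The aliens were pilot tested to obtain "stimuli that were perceived as relatively neutral, yet distinct". The compound alien is the same for everyone and plays no part in this point.

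Under Procedures, one alien is shown repeatedly as the CS+P before conditioning. In conditioning, the CS+P and CS+NP are each paired with the air puff on 75% of their trials and the CS- never is. The phase "will consist of 36 trials (12 CS^+^ _P_ trials, 12 CS^+^ _NP_, and 12 CS^-^ trials"). A person's alien therefore stays in one role throughout, and the counterbalancing can only be across participants.

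Under Statistical analysis plan (Hypotheses 1a and 2a), the conditioning-phase model is a three-way repeated measures MANOVA, run separately for expected relevance and attention: "pre-exposure groups will serve as the between-subjects factor with stimulus and trial being the within-subject factors". All main effects and interactions of these three factors are included. Follow-ups compare means by group and stimulus at each trial with a Bonferroni-adjusted alpha. The alien-to-role assignment is not among the factors.

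**The concern.** The design treats alien identity as a possible influence on outcomes, and the analysis does not use it. Counterbalancing removes the average confounding of alien with role, but it does not remove the variance. Each participant's CS+P minus CS+NP score also contains the difference between the two aliens that filled those roles. Without an assignment term, this known, design-controlled variation counts as random participant-by-stimulus error.

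The test most exposed is group × stimulus. It bears on the article's prediction that pre-exposure groups will differ more on the CS+P than on the other stimuli. What is at stake is the power of that test and of follow-up contrasts between stimuli.

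**Working it through.** **The plan's own figure.** The only sizing statement is: "The sample size of 180 participants was determined by an a priori power analysis". The article gives no alpha, power, effect size, SD, correlation or dropout, so 180 cannot be reproduced from it. The power figures below rest on assumptions.

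**Inputs from the article.** N = 180; four conditions ("Participants will be randomly assigned to one of the four between-subject conditions"); three aliens in three roles; model factors group, stimulus and trial.

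**Assumptions.** Equal cells (180 / 4 = 45 per group). Two-sided alpha 0.05. Total variance of one score on one trial set to 1, with correlation 0.5 between stimuli in the same person. Alien identity explains a share p, so t² = p and s² = 0.5 − p. The true effect gives 80% power for one group against another on CS+P minus CS+NP when only residual error is present. Assignment is unrelated to group.

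**Variance of the contrast.** Give the aliens effects −d, 0 and d. Their variance is t² = 2d²/3. The three possible pairs differ by d, d and 2d, so the mean squared difference is (d² + d² + 4d²)/3 = 2d² = 3t². Rotation makes the mean difference zero. Hence:

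- without the term: 2s² + 3t²
- with the term: 2s²
- inflation: 1 + 1.5(t/s)²

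**Power without the term.** Φ(2.802/√inflation − 1.960), where 2.802 = 1.960 + 0.842.

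| Alien share p | 2s² | 2s² + 3t² | Inflation | Power without term |
|---|---|---|---|---|
| 0 | 1.00 | 1.00 | 1.00 | 0.80 |
| 1% | 0.98 | 1.01 | 1.03 | 0.79 |
| 2% | 0.96 | 1.02 | 1.06 | 0.78 |
| 5% | 0.90 | 1.05 | 1.17 | 0.74 |
| 10% | 0.80 | 1.10 | 1.375 | 0.67 |

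**Gain from the term.** The normal formula ignores the degrees of freedom that the term uses. In simulations with six assignments and a 5-df term, power with the term was about 0.77 to 0.79 at every share. The comparison was about 0.74 against 0.79 at 5% and 0.67 against 0.79 at 10%. At 1–2% the gain was about 0 to 1 point. With no alien differences the term cost about 1 point (0.79 against 0.78).

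**Omnibus group × stimulus test.** This was a separate simulation: Wilks' lambda on two contrasts, four groups of 45, 2,000 runs and an assumed effect on the CS+P in one group.

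| t/s | Power without term | Power with term |
|---|---|---|
| 0 | 0.62 | 0.60 |
| 0.2 | 0.58 | 0.59 |
| 0.5 | 0.46 | 0.60 |
| 0.8 | 0.31 | 0.59 |

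A t/s of 0.2 is about a 2% share and 0.5 is a 10% share. The false-positive rate was 0.045 to 0.06 with or without the term.

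**Where the loss is smaller or absent.**

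- Group comparisons within one stimulus at one trial: the error already includes between-person variance, so the inflation is 1/(1 − p). At 5% this is 1/0.95 = 1.05, and power falls from 0.80 to 0.78.
- Group × stimulus × trial: an alien offset that is constant over trials cancels from changes across trials, so this test loses nothing unless alien effects themselves vary by trial.

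**The case against.** The strongest case against raising this is that nothing is wrong as stated. Counterbalancing does what the article claims for it, the test keeps its false-positive rate, and a blocking factor is optional. The document is a condensed journal article, and a fuller plan could add the term. The aliens were piloted to be relatively neutral as well as distinct. Being easy to tell apart does not mean that they draw different threat ratings or dwell times. If the alien share is 1–2% or less, the gain is negligible, and if it is zero the term costs about a point.

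Most of this stands, and it sets the weight of the point. What remains is that the article does not merely leave the model open. It names a three-way model and its terms, and that model omits a factor that the design sets and that the article gives a reason to control.

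A reader might also infer several stronger things that the documents do not support:

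- *That aliens rotate over roles within each person.* Pre-exposure and the fixed pairing schedule rule this out. If every alien did fill every role within a person, alien differences would cancel and no power would be lost: simulated power at t/s = 0.8 was then about 0.60 without the term and 0.59 with it.
- *That the group comparison is biased or its alpha inflated.* It is not, as long as assignment is unrelated to group, and nothing in the article suggests otherwise.
- *That the loss is larger because scores are averaged over several trials.* The planned conditioning-phase follow-ups are made trial by trial, so multi-trial power figures would match no stated analysis.
- *That a missed interaction would block the mediation models fitted by stimulus type.* That step depends on an interaction arising anywhere in Hypotheses 1a or 2a, which cover two mediators. One non-significant test does not settle it.

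**Conclusion.** The point holds as a minor efficiency improvement and not as a validity error. The stated conditioning-phase model omits the alien-to-role assignment. Because roles rotate across participants, stable alien differences then inflate the error of the group × stimulus test. The algebra is exact for a stable additive alien effect.

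The size is unknown because the article gives no alien variance. Under the single-trial assumptions set out above, it ranges from nothing worth having at a 1–2% share to about 5 points of power at 5% and about 12 at 10%. Piloting for neutrality makes the lower end plausible. The case for acting is that the factor is already known, the change is cheap and the possible loss is much larger than the possible cost.

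**What to change.** Add one sentence to the conditioning-phase analysis for Hypotheses 1a and 2a. The alien-to-role assignment enters the repeated measures MANOVA as a between-subjects blocking factor, with its interactions with stimulus and trial but not with group. The assignment × stimulus term absorbs stable alien differences, and the interaction with trial covers alien effects that change over the phase. Use the same model for the per-trial follow-up contrasts. In a mixed model, alien identity as a fixed effect does the same job.

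No new data are needed, provided each participant's assignment is kept in the analysis file. Three aliens in three roles allow 3! = 6 assignments, so the term uses at most 5 of the 180 − 4 = 176 between-subjects error degrees of freedom, and fewer if fewer assignments are used. If the aliens turn out not to differ, the price is about 1 point of power. State the term in advance, whether or not the aliens later appear to differ.
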